Clinical studies with topiramate suggest that it is effective as monotherapy or adjunctive therapy in PTSD. Two open-label studies demonstrated topiramate to be effective and to have a rapid onset of action. Berlant and van Kammen [27] have reported that topiramate decreased nightmares in 79% and flashbacks in 86% of civilian patients with chronic PTSD with improvement of nightmares in 50% and of intrusions in 54% of patients with these symptoms. A partial response was reported for 95% of patients at a dosage of 75 mg/day or less and in 91% of full responders at a dosage of 100 mg/day or less. The nonhallucinatory subgroup achieved a higher response rate (89%). In a prospective open-label study, Berlant [28] treated thirty three civilians with chronic PTSD, with topiramate as monotherapy or augmentation therapy. The PTSD Checklist-Civilian Version (PCL-C) total symptoms declined by 49% at 4th week, with similar subscale reductions for reexperiencing, avoidance/numbing, and hyperarousal symptoms. Topiramate suppressed nightmares in 79% and decreased symptoms of intrusions in 94% in those patients with these symptoms. There is only one double-blind, placebo- controlled study of topiramate as a monotherapy in PTSD. Tucker [29] conducted a 12-week, double-blind, placebo-controlled evaluation of topiramate as a monotherapy in thirty eight civilian PTSD patients. Patients in the topiramate group exhibited significant reductions in reexperiencing symptoms (CAPS cluster B: topiramate = 74.9%; placebo = 50.2%; p = .038) and reductions approaching statistical significance, based on a nominal p value, were noted in mean total Clinical Global Impressions-Improvement Scale scores (topiramate = 1.9 ± 1.2; placebo = 2.6 ± 1.1; p = .055). Although there was a reduction in total Clinician-Administered PTSD Scale (CAPS) score from baseline (topiramate = -52.7; placebo = -42.0), the difference was not statistically significant (p = .232). But not all studies found positive results, Lindley [30] in a double-blind, placebo-controlled study using topiramate as an augmentation therapy in forty male veterans with PTSD did not find significant treatment effects versus placebo. However, there was a high dropout rate from the study with 11 (55%) topiramate and 5 (25%) placebo subjects not completing the seven week treatment, with 40% of topiramate and 10% of placebo dropping because of adverse effects. Patients in the topiramate group that completed the study, had a significant improvement in the reexperiencing subscale of the CAPS suggesting efficacy for the patients that continued the medication.

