#### Active treatment phase

Those patients without improvement during the placebo trial, and do not show any laboratory and clinical condition exclusion criteria will be randomly assigned to receive either placebo or topiramate, in a 1:1 ratio using computer- generated code. The active and placebo pills will be identical. All research and clinical staff will be blinded to the randomized assignments.

Study medication will start at 25 mg/day once daily, at night, and will be increased 25 mg weekly, as tolerated, until complete or nearly complete efficacy is achieved or until 200 mg/day is reached. No other psychotropic medications will be allowed during the study, except for zolpidem (10 mg/day), if needed, for insomnia.

Study follow-up visits will be conducted at baseline, and weeks 1, 2, 3, 4, 6, 8, and 12.

Symptoms and side effects will be assessed, as well as measurement of systemic blood pressure and pulse rate in each visit by the investigator, who is blind to medication assignment. Compliance will be assessed by counting the amount of pills left in the bottle of medicine in each visit.

Treatment will be continued for 12 weeks (active treatment phase); then drug administration will be withdrawn gradually during 2 weeks with reductions of 25/50 mg every three days, according to the final dosage reached.

Patients will be assessed until completing 6 months during a follow-up period. If a patient showed a symptomatology worsening during the active treatment phase (12 weeks) when receiving active drug treatment, characterized by a one-point decrease at CGI -I or present serious adverse effects related to medication, he/she will be excluded from the study.

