### Statistical Analysis

All data will be analyzed by SPSS (version 13.0). The frequencies of nominal variables from all patients will be calculated. The data analysis will be conducted using a ANOVA comparing each scale during the 2 continuous measures from baseline and 12 weeks with a Between Subject factor was included as independent variable (treatment group). The confidence level that will be used for all comparisons will be 5% (p < .05). All observed Power as a type II error function will be presented with minimum values of significance for each comparison. CAPS scores from baseline and endpoint will be stratified according severity, as nominal data they will be compared using the chi-square test and the Fisher test when there were cells that counted less than five or at least one cell counted zero subjects. For missing data we will use the last observation carried forward strategy for an intention-to-treat analysis.

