Efficacy analyses will be performed in the intent-to-treat population of patients who received at least one dose of topiramate. The primary efficacy endpoint will be the change in PTSD Scale- CAPS total score from baseline to the final visit at 12 weeks, which will be compared between treatment groups. Missing efficacy data at 12 weeks will be imputed with the last observation carried forward. The secondary outcomes between groups will be comparing the Clinical Global Impressions (CGI), the Beck Depression Inventory (BDI), the Global Assessment of Function (GAF), and the PANAS scales. Other secondary analyses will include an evaluation after 24-weeks (12-week after last patient visit with drug) data with endpoint analyses between the treatment groups covarying for baseline scores. On all secondary outcomes, the Bonferroni correction will be applied for testing multiple variables. Response will be defined as a 20% improvement in the baseline CAPS total or positive symptom scores at 12 weeks and will be compared between treatment groups using a chi-square test. Proportions of patients completing the 12-week double-blind study will be compared between treatment groups using a chi-square test. Adverse events reported by 10% of patients in each treatment group will be compared using a chi-square test. Laboratory values, vital signs and physical examinations are going to be compared from baseline and in reference to normal ranges, and reported as normal or abnormal. Changes in body weight (lb), body mass index (BMI; kg/m2) at last visit in the 12-week dataset will be compared as mean changes between treatment groups using t-tests.

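### Removing patients from the study and then carrying their last CAPS forward to week 12 can bias the primary comparison when dropout differs between arms; the size and direction cannot be fixed from the document

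*Protocol article*

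**What the plan says.** The primary endpoint is fixed in the protocol article, Statistical Analysis: "The primary efficacy endpoint will be the change in PTSD Scale- CAPS total score from baseline to the final visit at 12 weeks". The same section gives the missing-data rule twice: "Missing efficacy data at 12 weeks will be imputed with the last observation carried forward" and "For missing data we will use the last observation carried forward strategy for an intention-to-treat analysis". The ANOVA is described as "comparing each scale during the 2 continuous measures from baseline and 12 weeks".

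The Active treatment phase section sets the removal rule. It opens "If a patient showed a symptomatology worsening during the active treatment phase (12 weeks) when receiving active drug treatment" and continues "characterized by a one-point decrease at CGI -I or present serious adverse effects related to medication, he/she will be excluded from the study". That section lists visits at baseline and weeks 1, 2, 3, 4, 6, 8 and 12, with symptoms assessed at each, but does not say which scales are used at which visit. It also describes assessment up to six months.

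The Aims make dropout per arm the measure of tolerability. The Background cites a controlled augmentation trial of topiramate with "11 (55%) topiramate and 5 (25%) placebo subjects not completing the seven week treatment", and with 40% vs 10% leaving for adverse effects.

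**The concern.** A patient removed for worsening or for a serious drug-related adverse effect has no week-12 CAPS under the rule as written. Missingness is therefore tied to response and tolerability. The gap is filled by an earlier score that the analysis treats as an observed week-12 value, with no allowance for the uncertainty of the imputation.

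The cited 12-week monotherapy trial reports falls in CAPS of 52.7 points on topiramate and 42.0 on placebo. Where scores fall that much in both arms, a score frozen early understates the change the patient would have shown by week 12. If one arm loses more patients, or loses them earlier, the between-arm contrast reflects dropout as well as efficacy. Unequal dropout is foreseeable here, because the plan cites an example of it and measures it as an outcome.

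**Working it through.** The plan gives no figure for the effect of missing data, so there is none to reproduce. The check asks how far carry-forward moves the contrast over a plausible range.

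**Inputs**
- 36 patients per arm (Sample Size), taken as stated.
- CAPS changes of -52.7 and -42.0, p = .232, 38 patients: the 12-week monotherapy trial in the Background.
- Dropout of 55% vs 25% in total, and 40% vs 10% for adverse effects: the seven-week augmentation trial in male veterans in the Background. 30% vs 20% is an assumed milder case.
- SD of change (assumed): p = .232 with an assumed 19/19 split gives t = 1.216 on 36 df. SE = 10.7/1.216 = 8.80. SD = 8.80/√(2/19) = 27.1.
- f, the share of the 12-week change already reached at the last CAPS: not in the document, so varied from 0 to 1 and taken as equal in both arms.

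**Formula.** Expected mean change in an arm = full change × [(1 - d) + d·f], with d the dropout proportion. If both arms truly change by -42, the false difference is 42 × (d_topiramate - d_placebo) × (1 - f).

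**Equal true changes of -42** (positive = against topiramate; error = two-sided rejection rate of a t-test on change in simulated trials)

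| Dropout | f | Topiramate | Placebo | False difference | Error |
|---|---|---|---|---|---|
| 55%/25% | 0 | -18.9 | -31.5 | 12.6 | about 45% |
| 55%/25% | 0.5 | -30.45 | -36.75 | 6.3 | 19 to 20% |
| 55%/25% | 0.75 | -36.2 | -39.4 | 3.1 | about 8% |
| 30%/20% | 0 | -29.4 | -33.6 | 4.2 | about 9% |
| 30%/20% | 0.5 | -35.7 | -37.8 | 2.1 | 6 to 7% |
| 30%/20% | 0.75 | -38.85 | -39.9 | 1.05 | about 5% |

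Dropout of 40%/10% has the same 30-point gap, so it gives the same false differences. Equal dropout gives none.

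**Check of the 45%.** At f=0 the variance in an arm is (1 - d)(27.1² + 42²) - [(1 - d)·42]², about 767 and 882. SE = √((767 + 882)/36) = 6.77, and 12.6/6.77 = 1.86 against a critical value of 1.99. That agrees with a rejection rate near 45%.

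**True changes of -52.7 and -42.0, 55%/25%.** Without dropout the contrast is -10.7, and about 38% of trials significantly favour topiramate.
- f=0: -23.7 vs -31.5, contrast +7.8, about 0% favour topiramate.
- f=0.5: -38.2 vs -36.8, contrast -1.5, about 4%.
- f=0.75: -45.5 vs -39.4, contrast -6.1, about 17%.

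For scale, the systematic review cited in the Background gives a pooled drug-placebo difference of 5.76 CAPS points.

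**The case against.** **The illustration joins two different trials.** The CAPS changes come from 12-week civilian monotherapy, for which the article reports no dropout. The dropout comes from seven-week augmentation in male veterans, for which it reports no CAPS change. The planned trial resembles the first. The article also does not say how that trial handled its own missing scores; if they were carried forward, the illustration counts dropout twice. This stands: 55%/25% shows that unequal dropout can happen and does not forecast it.

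**A reader might infer that carry-forward here means baseline carried forward,** so that 12.6 points, 45% error and a reversed sign are the expected result. The document does not support that. Two measures enter the ANOVA, but that is not an assessment schedule, and an article may leave the scales used at each visit to the full protocol. The f=0 rows are a worst case.

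**A reader might infer that the type I error is necessarily far from 5%.** At 30%/20% with half or more of the change retained, the bias is about 1 to 2 points and the error about 5 to 7%.

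**A reader might infer that topiramate is always penalised.** A patient removed while worsening has a score frozen before any further worsening, which can favour the arm that loses such patients.

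**The excess rejections in this scenario favour placebo,** so it does not show a raised risk of falsely claiming benefit. That is correct.

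Sensitivity analyses may sit in an analysis plan not shown, and their absence is not held against the plan. None of this removes the core point: the article itself fixes carry-forward as the primary rule, alongside a removal rule tied to outcome and tolerability.

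**Conclusion.** The concern holds as a risk of bias whose size and direction the document does not allow one to determine. With equal true changes of -42, the false difference runs from about 1 point (30%/20% dropout, f=0.75) to 12.6 points (55%/25%, f=0). It exceeds the 5.76-point pooled effect only with a large dropout imbalance and f at about 0.5 or below. If topiramate patients leave more often while CAPS is still improving, the main consequence is lost power for the superiority hypothesis.

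The figures assume an SD near 27, the same f in both arms, dropout unrelated to the patient's own eventual change, and that patients who leave would otherwise have reached the full change of their arm. The last assumption matters most where the drug is taken to work.

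The removal rule also needs reconciling within the document. Its worsening limb is worded for patients on active drug, although staff are blinded. It describes worsening as a decrease on CGI-I, whereas the Measures section scores worsening with higher values. As written, it is unclear whose data would go missing.

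**What to change.** 1. Separate stopping study drug from leaving the study. Keep patients who stop in follow-up and obtain a week-12 CAPS from all who consent, using visits already scheduled. This changes no treatment-stopping rule. It is the most important step, because scores not collected cannot be recovered by any analysis.
2. Replace carry-forward as the primary method with ANCOVA on week-12 CAPS adjusted for baseline, with multiple imputation by arm using baseline CAPS and any interim CAPS or CGI collected. A likelihood-based mixed model is an alternative if interim CAPS exist. With only baseline and week-12 CAPS, it adds no post-baseline information on patients who drop out.
3. Keep carry-forward only as a sensitivity analysis.

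Cost: some patients will decline the off-drug week-12 CAPS, and the analysis needs modest extra programming.

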### Sample Size

The number of subjects calculated for the trial is 72, being 36 on each cell. The sample size was calculated considering a 5% probability of type I error (significance level), and 20% for type II error (power test of 80%), on a bi-caudal test. To the calculation we use an average of 60% for response from PTSD for active drugs, based on published literature, and 30% of placebo response.

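### The significance level for the response comparison that set the sample size is not settled, and neither possible reading gives that comparison the printed 80% power

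*Protocol article*

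**What the plan says.** **Sizing.** The Sample Size section of the protocol article gives one basis for the number of patients: "we use an average of 60% for response from PTSD for active drugs, based on published literature, and 30% of placebo response". The error rates are set by "considering a 5% probability of type I error (significance level" and "20% for type II error (power test of 80%), on a bi-caudal test", and the result is "The number of subjects calculated for the trial is 72, being 36 on each cell". Allocation is equal (Active treatment phase: "in a 1:1 ratio using computer- generated code").

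**Primary endpoint.** The second paragraph of the Statistical Analysis section, in line with the abstract, names one: "The primary efficacy endpoint will be the change in PTSD Scale- CAPS total score from baseline to the final visit at 12 weeks".

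**Secondary outcomes and multiplicity.** The same paragraph names CGI, BDI, GAF and PANAS as secondary outcomes, adds a 24-week evaluation, and then says: "On all secondary outcomes, the Bonferroni correction will be applied for testing multiple variables". It gives no number of tests.

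**Response.** The next sentence defines response and assigns it a chi-square test between groups at 12 weeks. It calls response neither primary nor secondary.

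**General level.** The first paragraph of the section sets 5% for all comparisons.

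**The concern.** A power figure holds only for the significance level at which the test is carried out. Here the outcome that fixed the number of patients is not the primary endpoint, and it stands directly after a rule that tightens the level for every secondary outcome, with no exemption. The sizing assumes that no such tightening applies. If it does apply, the level could be 0.05/4 to 0.05/6 or stricter, and a true difference of 60% against 30% could be missed about half the time. If it does not apply, the text should say so, because another reader could reasonably apply it. Leaving this open also means that the level for response could be chosen once the data are known.

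**Working it through.** **Inputs from the protocol article.** n = 36 per arm; p1 = 0.60, p2 = 0.30; two-sided 5%; target power 80%; chi-square test.

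**Input that the article does not give.** The number of tests k in the Bonferroni family, taken here as an assumption:
- four named measures plus response: k = 5;
- k = 6 if the two CGI scales count separately;
- k = 4 if PANAS, which the Measures section does not describe, is dropped;
- k = 10 if the five tests are counted at both 12 and 24 weeks.

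Smaller values are shown for range.

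**Step 1: the plan's own figure.** The pooled normal formula is

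n per arm = [z(1−α/2)·√(2·p̄·(1−p̄)) + z(0.80)·√(p1(1−p1) + p2(1−p2))]² / (p1−p2)²

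With p̄ = 0.45:
- √(2 × 0.45 × 0.55) = 0.7036
- √(0.24 + 0.21) = 0.6708
- n = (1.960 × 0.7036 + 0.8416 × 0.6708)² / 0.09 = (1.379 + 0.565)² / 0.09 = 41.97, so 42 per arm, 84 in total.

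Unpooled variance gives 40 per arm (80), the arcsine formula 42 (84), and the continuity-corrected formula 49 (98). None gives 36 per arm.

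**Step 2: power at 36 per arm and 5%.**

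Power = Φ[(|p1−p2|·√n − z(1−α/2) × 0.7036) / 0.6708] = Φ[(0.30 × 6 − 1.379) / 0.6708] = Φ(0.628) = 73.5%.

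Exact enumeration of the two binomial distributions with the uncorrected chi-square test gives 72.7%. The shortfall from 80% is 80 − 72.7 = 7.3 points and has nothing to do with Bonferroni.

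**Step 3: power at 36 per arm if response is tested at 0.05/k.** For example, at k = 5: z = 2.576, and Φ[(1.8 − 2.576 × 0.7036) / 0.6708] = Φ(−0.018) = 49.3%.

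| k | level | exact chi-square | normal approximation |
|---|---|---|---|
| 1 | 0.0500 | 72.7% | 73.5% |
| 2 | 0.0250 | 63.3% | 63.0% |
| 3 | 0.0167 | 55.5% | 56.9% |
| 4 | 0.0125 | 53.8% | 52.5% |
| 5 | 0.0100 | 53.5% | 49.3% |
| 6 | 0.0083 | 46.4% | 46.7% |
| 10 | 0.0050 | 43.6% | 39.7% |

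The exact column falls in uneven steps because the counts are discrete.

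**Step 4: the part due to the level alone.** From 72.7%, the loss is 72.7 − 63.3 = 9.4 points at k = 2, 72.7 − 53.8 = 18.9 at k = 4, 72.7 − 46.4 = 26.3 at k = 6, and 72.7 − 43.6 = 29.1 at k = 10.

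**Step 5: cost of testing response only after the primary test.** Assume that improvement is normally distributed with equal spread in both arms, and that a common cut-off gives 60% and 30% responders. The standardised difference is then 0.253 + 0.524 = 0.78. In 100,000 simulated trials the primary comparison was significant in 90.3%, response at 5% in 73.0%, and both in 71.9%. The gate costs 73.0 − 71.9 = 1.1 points.

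**The case against.** A reader might infer that the plan definitely tests response at a Bonferroni level, so that its power definitely falls to about a half. The documents do not support that. Response is not among the four named secondary outcomes. Its sentence follows the Bonferroni rule, but so do those on completion, adverse events and weight change, so position proves little. The Aims of the Study define response within the first aim, on efficacy, and the Research Goals leave it out of the secondary goals. The first paragraph of the Statistical Analysis section sets 5% for all comparisons; on that reading the sizing level and the testing level agree. The number of tests is nowhere stated, and a full list of the family is a detail that an article may leave to the analysis plan. All of this stands, and it makes every figure below 73% conditional.

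It does not remove the point. The general 5% cannot settle the matter alone, because taken literally for every comparison it would cancel the Bonferroni rule as well. The first aim defines response but does not make it primary. And if response is tested at 5%, power is still about 73%, not 80%.

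A second tempting inference is that the main efficacy conclusion is at risk. It is not on this ground: the CAPS change is the single primary endpoint and lies outside the correction.

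**Conclusion.** The point holds in limited form. The article fixes a sizing level, a correction rule and a general 5% level, and together they do not determine the level for the comparison that set the sample size. On neither reading does that comparison have the printed 80%. At 5% it has about 73%, which rests only on the article's own inputs and an uncorrected chi-square test. Within a Bonferroni family it has about 54% to 46% for four to six tests, with 63% for two and 44% for ten; these rest on an assumed number of tests and on response being in the family, which is an inference. A drop from 80% to these values should not be attributed wholly to the correction, since 7.3 points of it arise at 5% already. It deserves correction but does not undermine the primary analysis. Confidence is moderate, because the status of response is unstated rather than stated wrongly.

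**What to change.** In the Statistical Analysis section, state that 12-week response is tested at two-sided 5% only if the primary CAPS comparison is significant at two-sided 5%, and that Bonferroni applies to the remaining secondary outcomes. This fixed sequence controls the overall error rate across those two tests. In the Sample Size section, replace 80% with about 73%.

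If the sponsor prefers to keep response in the Bonferroni family, the Sample Size section should instead give the number of tests, the corrected level and the power that 36 per arm has there, for example about 53% at 0.05/5.

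Either route takes two or three sentences and no extra patients. The costs are that response can be claimed only after a significant primary result (about 1 point of power under the normal model above) and that the stated power looks less favourable. Keeping 80% for response would be a different decision: by the pooled normal formula it needs 42 per arm (84) at 5%, or 60 per arm (120) at 0.05/4.

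### The 10% threshold for comparing adverse events applies to each arm, so an event common on topiramate but rare on placebo gets no planned comparison

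*Protocol article*

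**What the plan says.** The Statistical Analysis section of the protocol article gives one rule for comparing individual adverse events between arms: "Adverse events reported by 10% of patients in each treatment group will be compared using a chi-square test". The arm size comes from the Sample Size section: "The number of subjects calculated for the trial is 72, being 36 on each cell".

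No other part of the article sets a between-arm rule for single event types:

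- Aims of the Study and Research Goals measure tolerability through the dropout rate.
- Active treatment phase has side effects assessed at every visit, without saying how they are compared.
- Statistical Analysis has the frequencies of nominal variables calculated. It treats 12-week completion, laboratory values, vital signs, physical examination, weight and body mass index separately, and none of these carries a 10% threshold.

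**The concern.** A frequency threshold for testing adverse events is ordinary practice and keeps isolated reports out of the tests. The difficulty is that this one depends on the placebo count as well as the topiramate count. The pattern that points most clearly to a drug effect is an event frequent on active treatment and nearly absent on placebo, and a rule requiring 10% in both arms removes that pattern. Events with a sizeable background rate pass.

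What is at stake is the formal comparison of individual adverse events. The rule is stated in the article, so this is not detail left to a fuller document. An analyst who follows it would omit the most unequal events from testing. One who suspects that *either* was meant would have to choose between the readings, possibly after seeing the data.

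**Working it through.** **Inputs.** From the article: 36 patients per arm (Sample Size) and a 10% threshold in each arm (Statistical Analysis). Assumed: the true event rates, because the article gives none by event type. I use 30% on topiramate and 0% to 10% on placebo.

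**The plan's own figure.** The adverse-event rule has no computed figure to reproduce. The 36 per arm is taken as stated. For the record, the usual two-sided formula with pooled variance, at 5% significance and 80% power for 60% against 30%, gives 42 per arm. That is a separate matter and this point does not depend on it.

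**Step 1: the threshold as a count.** 0.10 × 36 = 3.6, so at least 4 patients are needed. Under the rule as written, both arms need 4 or more.

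**Step 2: observed results that would not be compared.** Each has 3 or fewer placebo cases. Fisher's exact test, two-sided:

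| Topiramate | Placebo | Fisher p |
|---|---|---|
| 12/36 | 0/36 | 0.00016 |
| 12/36 | 3/36 | 0.018 |
| 14/36 | 3/36 | 0.0046 |
| 18/36 | 3/36 | 0.00018 |

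**Step 3: chance that an event is compared.** Let A = P(X ≥ 4) for X ~ Bin(36, topiramate rate) and B = P(Y ≥ 4) for Y ~ Bin(36, placebo rate). With independent arms:

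- threshold in each arm: A × B
- threshold in either arm: 1 − (1 − A)(1 − B)

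At 30% on topiramate, A = 0.9982. For a 5% placebo rate, P(Y ≤ 3) = 0.1578 + 0.2990 + 0.2754 + 0.1642 = 0.8963, so B = 0.1037. The rule as written then gives 0.9982 × 0.1037 = 0.1035. The *either* rule gives 1 − 0.0018 × 0.8963 = 0.998.

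| Assumed placebo rate | B | Compared, each | Compared, either |
|---|---|---|---|
| 0% | 0 | 0 | 0.998 |
| 2% | 0.0057 | 0.0056 | 0.998 |
| 5% | 0.1037 | 0.1035 | 0.998 |
| 8% | 0.3246 | 0.324 | 0.999 |
| 10% | 0.4915 | 0.491 | 0.999 |

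The placebo rate drives the result. Raising the topiramate rate to 40% moves the 5% row only from 0.1035 to 0.1037.

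**Step 4: differences lost.** Summing over all possible pairs of counts, true rates of 30% against 2% give Fisher p < 0.05 with probability 0.907, and 99.8% of those results fail the rule as written. At 30% against 5% the figures are 0.759 and 95.7%. At 40% against 10% they are 0.800 and 60.5%.

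**Step 5: choice of test.** With equal arms, the expected count in each event cell is half the total number of events. Under the rule as written the total is at least 8, so an expected count falls below five only for 4 against 4 (expected 4.0) and 4 against 5 (4.5). Neither is near significance. Under the *either* rule, totals of 4 to 9 can all occur. At 4/36 against 0/36 the expected count is 2.0, and uncorrected chi-square gives p = 0.040 against 0.115 by Fisher. The test therefore matters once the threshold is corrected.

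**The case against.** **Loose wording.** The sentence lacks *at least*, and *each* may be a clumsy way of saying *either*. That is possible, and the intention cannot be established. Nothing in the article supports the milder reading, though, and the sentence needs the same edit under both.

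**Stronger readings the article does not support:**

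- *The tolerability aim is compromised.* A reader might infer this because tolerability is one of the two aims. Aims of the Study defines it through dropout, and completion is compared between arms with no 10% filter. That analysis is untouched, as are those of laboratory values, vital signs and weight.
- *Large imbalances would be hidden.* The article does not say that events below the threshold go unreported, and a 12/36 against 0/36 split would be plain in a frequency listing. What is lost is the planned comparison.
- *Drug-specific events would never be compared.* This holds only when placebo has 3 or fewer cases. At an assumed true placebo rate of 10%, chance alone brings such an event over the threshold in about half of trials.
- *The earlier augmentation trial in the Background illustrates the loss.* It reports "40% of topiramate and 10% of placebo dropping because of adverse effects". Those are discontinuations, not rates of a single event type, and observed proportions of 40% and 10% would meet the threshold.
- *Chi-square here contradicts the plan's own Fisher rule.* The rule, "the Fisher test when there were cells that counted less than five", is written for CAPS severity categories, so there is no contradiction.

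**Conclusion.** The concern holds as a fault in the stated rule. As written, an adverse event with 3 or fewer placebo cases out of 36 receives no planned between-arm comparison, whatever its frequency on topiramate. For an event at 30% on topiramate, the chance of being compared is about 0.6%, 10% and 49% at placebo rates of 2%, 5% and 10%, against at least 0.998 under an *either* rule.

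The count of 4 rests on the planned 36 per arm and on a literal reading of *each*. The probabilities also rest on assumed event rates and on independent arms. The effect is confined to formal comparisons of individual adverse events.

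**What to change.** Replace the sentence with, for example: *Any adverse event that at least 10% of patients in either arm report will be compared between arms by a chi-square test, or by Fisher's exact test where an expected count is below five.* The Fisher clause belongs in the same edit because small or zero placebo cells become common under the new threshold.

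The cost is a few more rows and tests in the safety table, and so a few more chances of a nominally significant difference. It needs no new data and no change to sample size or trial conduct.

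### Laboratory values and vital signs are to be reported as normal or abnormal with no placebo comparison named, which discards small to moderate within-range changes

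*Protocol article*

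**What the plan says.** All references are to the protocol article.

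- **Laboratory values, vital signs, physical examinations** (Statistical Analysis): they will be "compared from baseline and in reference to normal ranges, and reported as normal or abnormal". The comparators are each patient's baseline and the reference range, and the reporting form is two categories. No treatment-group comparison and no test is named.
- **Body weight and BMI** (next sentence of the same section): changes "at last visit in the 12-week dataset will be compared as mean changes between treatment groups using t-tests".
- **Adverse events and completion of the 12 weeks** (same section): compared between groups by chi-square test.
- **Data collected** (Active treatment phase): each visit includes "measurement of systemic blood pressure and pulse rate in each visit by the investigator". The laboratory panel is listed under Screening Phase. The article shows no on-treatment laboratory schedule, although the analysis sentence presupposes later values.
- **Tolerability** (Aims of the Study, Research Goals): studied through the dropout rate in each group.

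**The concern.** Blood pressure, pulse and the laboratory analytes are numeric. Reduced to normal or abnormal, a value that moves a long way but stays inside its range counts as no change. Patients are randomised only if no laboratory or clinical exclusion applies, so it is reasonable to expect most values to start in range. The article gives no laboratory thresholds to confirm this.

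A comparison with baseline alone also cannot separate a drug effect from time, regression to the mean or whatever happens on placebo. The trial has a concurrent placebo arm that removes this ambiguity, and the next sentence uses it for weight and BMI.

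What is at stake is how informative the description of vital signs and laboratory values is. A small number of abnormal results in two arms of 36 says little about whether topiramate shifts these measures.

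**Working it through.** **The plan's own figure.** The article has one computed figure, the sample size: "The number of subjects calculated for the trial is 72, being 36 on each cell". Its inputs are "5% probability of type I error (significance level" of 5%, "20% for type II error (power test of 80%), on a bi-caudal test", 60% response on active drug and "30% of placebo response". The usual pooled formula gives

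n = [1.96·√(2·0.45·0.55) + 0.8416·√(0.60·0.40 + 0.30·0.70)]² / 0.30² = (1.379 + 0.565)² / 0.09 ≈ 42 per arm.

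So 36 does not reproduce; power at 36 is about 73.5%. That is a separate matter and bears on this point in neither direction. I take 36 per arm as given.

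**Assumptions not in the article.** One measure at a time, normally distributed with equal SD in both arms; reference range = mean ± 1.96 SD; topiramate shifts the mean by d SD and placebo by nothing; no loss of patients; two-sided 5%.

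**Step 1: abnormal rate after a shift.** P(abnormal) = 1 − Φ(1.96 − d) + Φ(−1.96 − d).

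- d = 0: 2.5% + 2.5% = 5.0% (1.8 of 36 expected)
- d = 0.5: 7.2% + 0.7% = 7.9% (2.8 of 36)
- d = 0.7: 10.4% + 0.4% = 10.8% (3.9 of 36)
- d = 1.0: 16.9% + 0.2% = 17.0% after rounding (6.1 of 36)
- d = 1.5: 32.3% + 0.0% = 32.3% (11.6 of 36)

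**Step 2: power of normal/abnormal between arms.** Sum the binomial probabilities over all 37 × 37 outcomes with p ≤ 0.05, using Fisher's test when an expected count is below 5 and chi-square otherwise. The article names no such test for these measures, so this is generous to it.

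**Step 3: power of a t-test on mean change.** The SD of change is SD·√(2(1 − r)), where r is the correlation between baseline and last visit. For r = 0.5 it equals the SD; for r = 0.7 it is 0.775 SD. The noncentrality is d/√(2(1 − r)) · √(36/2), with 70 degrees of freedom. For d = 0.5 this is 2.12 (r = 0.5) or 2.74 (r = 0.7).

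| Shift | Normal/abnormal | Mean change, r = 0.5 | Mean change, r = 0.7 |
|---|---|---|---|
| 0.5 SD | 1.4% | 55.3% | 77.1% |
| 0.7 SD | 5.0% | 83.4% | 96.6% |
| 1.0 SD | 25.7% | 98.7% | >99.9% |
| 1.5 SD | 88% | about 100% | about 100% |

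**Step 4: sensitivity to the background rate.** Count only values beyond the limit in the direction of the shift, and let the placebo abnormal rate run from 1% to 10%. Fisher power is then 0.1–18% (0.5 SD), 0.7–40% (0.7 SD), 8–77% (1.0 SD) and 67–99% (1.5 SD). The t-test figures at r = 0.5 are unchanged. With 27 per arm (an assumed 25% loss), the 0.7 SD figures are 0.2–25% against 71%, and the 1.0 SD figures 3–60% against 95%.

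**Step 5: precision of the better summary.** The half-width of the 95% interval for the difference in mean change is about 1.994·√(2/36) = 0.47 SD at r = 0.5. A non-significant t-test therefore does not exclude a 0.5 SD shift, which is why the interval should be shown.

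**The case against.** The strongest objection is that this is a condensed article. The layout of safety tables is commonly left to the full protocol or analysis plan, and silence about arms is not exclusion. That stands against one tempting inference, that these measures will be compared only with baseline and reference ranges: the article does not rule out tabulation by arm. It does not dispose of the point, because the sentence fixes a reporting form, and two-category counts by arm would still lose the power shown above.

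A reader might also infer that a real shift would almost never be seen, or would be reported as no safety signal. Neither is supported. The first fits only small to moderate shifts with a low background abnormal rate; at 1.5 SD detection is likely. The second is nowhere in the text. Tolerability is defined through dropout, and adverse events, completion, weight and BMI keep between-group tests, so the safety comparison as a whole is not lost.

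Two further objections stand in part. The power figures rest on assumed distributions, and the article identifies no shift that would matter for any analyte, so they illustrate the loss of information and do not predict a missed harm. And testing at least 12 measures (two blood pressures, pulse, eight named chemistry and thyroid values, one or more blood-count items) at 5% would, if they were independent, give 1 − 0.95¹² = 46% chance of at least one false signal. That argues for intervals labelled descriptive, not for keeping two categories alone.

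**Conclusion.** The point holds in a limited form. For laboratory values and vital signs the article fixes a two-category report against baseline and reference range and names no comparison with placebo, while it does name one for the neighbouring safety measures. Under the stated assumptions the loss is large for shifts of 0.5 to 1.0 SD and small at 1.5 SD.

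The result depends on normality, the ± 1.96 SD range, complete data at 36 per arm, the correlation and the background abnormal rate; a higher background rate narrows the gap. The point is firmest for blood pressure and pulse, which are measured at every visit. For laboratory values it depends on post-baseline data whose timing the article does not show. It is worth changing before analysis but touches no primary or listed secondary outcome.

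**What to change.** In Statistical Analysis, extend the treatment of weight and BMI to the other numeric safety measures. For blood pressure, pulse and, where post-baseline values exist, each laboratory value:

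- give the mean change from baseline to the last visit by arm;
- give the between-group difference with its 95% confidence interval, labelled descriptive;
- base any statement about the absence of an effect on the limits of that interval.

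Keep the normal/abnormal counts, shown by arm, as a table beside this. Leave physical examination findings as normal or abnormal, which suits them.

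The cost is one more safety table and more unadjusted comparisons, which the descriptive label should make plain. No measurements are needed beyond those the analysis section already relies on.
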